#### 5.6. Check each age range applicable to participants or data/specimens.

|                                               |
|-----------------------------------------------|
|  Ages 0-7             |
|  Ages 8-17 |
|  Ages 18+  |
|  Other; specify:      |

#### 5.7. Describe study procedures.

We will engage in six categories of data collection procedures: facility assessment; register data extraction; health worker interviews; patient interviews with a cohort of pregnant women recruited from antenatal care clinics; delivery observation; and process evaluation.

**Facility assessment.** Enumerators will conduct a facility assessment at the time of baseline. No individually identifiable information will be collected in the facility assessment.

- 1) At the start of data collection, the enumerator will identify who holds the position of facility In-Charge and Head Midwife and schedule appointments with them.
- 2) During this meeting, the enumerator will share the purpose and content of the facility audit and ask if health workers that are familiar with the facility operations are willing to meet for an interview. These health workers may include the In-Charge, Head Midwife, and pharmacists. Interviews will be scheduled during a time when these staff are not busy with other duties and have had enough time to update the register from the most current numbers.
- 3) The enumerator will meet designated staff at the scheduled time. The enumerator will identify a quiet and private space where the enumerator and staff member will sit together for the duration of the interview. The enumerator will ask the required information and ask the staff member any clarifying questions. Each respondent will be interviewed individually and privately and preferably outdoors. The interviews may be recorded for quality control purposes.

**Register data extraction:** Enumerators will capture data on delivery outcomes, complications, and incidence of morbidity and mortality from facility registers in consultation with facility in-charges and head midwives. Enumerators will complete the Register Data Form by copying the information from the facility registers (e.g., the MOH 333 Maternity Register) in the baseline and the endline.

- 1) In the baseline and the endline, enumerators will collect register data without any personally identifiable information (e.g., name, date of birth, phone number, etc.). Register data entered from the period that covers 12 months prior to the baseline and up to 12 months after the endline will be extracted.

**Health worker interviews.** Enumerators will interview about 2 - 8 health workers per facility at both the baseline and the endline:

- 1) The enumerator will approach all health workers that meet the inclusion criteria at the maternity ward. The enumerator will approach health workers individually, share with them the purpose of the interview, and ask whether they are willing to participate.
- 2) The enumerator will schedule an interview with each health worker at a time when the staff is not busy with other duties.
- 3) The enumerator will meet each health worker at the scheduled time. The enumerator will identify a quiet and private space where the enumerator and the health worker will sit together for the duration of the interview. The enumerator will ask the required information and ask the staff member any clarifying questions. Each respondent will be interviewed individually and privately, and preferably outdoors. The interviews may be recorded for quality control purposes.

**Patient interviews with a cohort of pregnant women:** we will recruit pregnant women who visit health facilities for antenatal care. One or two enumerators will be stationed outside of the antenatal care clinic in each facility to enroll prenatal patients. Pregnant women who consent to participate in the study will be contacted by phone toward the end of their pregnancy and at about 7 – 8 weeks postpartum for follow-up surveys. Women from intervention facilities who agree to receiving text messages will be enrolled in the PROMPTS program by Jacaranda Health. Procedures for data collection are as follows:

- 1) The enumerators will be on site before the antenatal care clinic is open to see patients.
- 2) Enumerators will approach women before or after they receive antenatal care (e.g., to wait for her providers or right after the completion of her visit) and recruit them to participate in the study. Enumerators will obtain women's consent and conduct a short survey on health care utilization, knowledge, and demographics (including women's contact information for follow-up calls). This will be done in a private space to protect participants' privacy and preferably outdoors. If the respondent does not have a mask, the enumerator will provide one.
- 3) Enumerators will also make a short announcement periodically to those in the waiting bay/queue that they are recruiting participants for a research study and can explain the details of the study for those interested outdoors.
- 4) Enumerators will conduct two short follow-up interviews by phone. The first interview will occur towards the end of pregnancy and the second interview will occur at around 7- to 8-week postpartum. These interviews will contain questions about women's health care utilization, health knowledge, self-efficacy, health outcomes, and experience with the intervention (if applicable). Enumerators will confirm the identity of the participant before proceeding with the phone interviews. Participants who complete surveys will receive a small SMS credit. The phone interviews may be recorded for quality control purposes.

**Delivery observations:** medically trained enumerators will observe labor, delivery, and postpartum care and record information on quality of care during the endline period.

- 1) Enumerators, with the aid of the maternity in-charge, will decide in advance where to sit in different parts of the maternity ward so as to be able to observe the actions of the health workers, but be out of the way and non-disruptive.
- 2) Introduction and consent:
  - a. Upon arrival of a woman in labor, an enumerator will join the health staff in approaching and greeting the woman. Following the first examination and confirmation of admission, the enumerator will wait until an appropriate moment to begin consent procedures. The enumerator will not approach a woman for consent who is not stable or able to focus on the consent process. The enumerator will ask for the woman's consent before her first examination for her care to be observed and her records to be transcribed from the facility records (e.g., maternity register). The enumerator will not record information about the woman until consent has been given.
  - b. In some situations, a woman may be unable to give consent upon arrival to the facility but may later be sufficiently stable to give consent. In this situation, an enumerator may approach the woman once she is stable and able to give consent. As above, the enumerator will not record information about the woman until consent has been given.
- 3) Collecting clinical quality observation data:
  - a. If the woman consents to participate in the study, the enumerator will thank her and inform her that he/she and the other enumerators will not be giving any care to her during the duration of her delivery, but will only be present as observers.
  - b. Enumerators will avoid speaking to patients or health workers, and will avoid sudden movements that may draw any attention.
  - c. The enumerator will follow the staff and woman to the maternity ward.
  - d. The enumerator will observe labor and delivery for as long as it is on-going, up until time of discharge from the facility, time when a patient is referred out and leaves the facility, or when a patient is going to receive a Cesarean section.
  - e. The enumerator may use the patient chart, partograph, the woman's antenatal care book, bill, or any other written notes or records to complete the observation tool. In cases when the antenatal care book is used, the enumerator will politely request for the book from the patient. The enumerator will only ask for the book at a time when it is not disruptive to other processes.
  - f. If the enumerator is satisfied with the checklist, all information will then be fed into the tablet. Information in the tablet must be identical to that on the paper form.
- 4) Protocol in case of emergencies:
  - a. Protocol for enumerators will be to not intervene in the care provided to the woman, unless in the case of a life-threatening emergency that could benefit directly from the enumerator's involvement. Should the enumerator observe gross mismanagement of a patient and he/she feels that the situation is life threatening, the enumerator may offer advice and/or assistance.
  - b. If an enumerator intervenes, they will do so in their capacity as a medical expert, not as a research observer. They must be medically qualified to intervene in the specific situation, that is, have had the necessary training to be qualified to provide care. If

possible, the enumerator should call the study team leader for advice on the way forward before intervening. All instances of enumerators offering assistance to health workers will be well documented. Enumerators should frequently but politely remind the health workers at the facility that they are only observers and not present to provide care or assistance.

**Process evaluation:** We will use program administrative data to assess the implementation of the intervention until study activities are complete in intervention facilities. This data is routinely collected by Jacaranda Health.

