## 2. Background and Significance

### 2.1 Provide the scientific background and rationale for the research.

Reducing maternal and newborn mortality and morbidity remains a major public health priority in many countries in sub-Saharan Africa (SSA). In Kenya, maternal mortality and neonatal mortality remain high at 3.4 and 21 per 1,000 live births respectively. A recent study suggests that more than half of the avertable maternal and neonatal deaths in low- and middle-income countries could be amenable to better quality care, but two key challenges limit health systems’ ability to improve quality of care and patient health outcomes in Kenya.

The first challenge is that providers do not always deliver high-quality care that could avert or mitigate life-threatening pregnancy and postpartum complications due to lack of knowledge and skills. Research has shown that training in emergency obstetric care is effective in improving some maternal

and neonatal outcomes, but one-off dissemination of guidelines is often insufficient to sustain improvement in providers' knowledge or practice in low-resource settings. Mentorship programs that provide hands-on and longer-term support to health workers aim to achieve sustained improvements in quality of care through developing health workers' skills and competencies. However, evaluations of their effectiveness often focus on provider knowledge or practice alone without assessing health outcomes and very few studies are conducted in SSA using experimental designs.

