#### Enumerators:

- Strong writing and analytical skills and able to work with minimum supervision.
- Experience working in research and field data collection
- Understanding and experience in collecting electronic data using tablets
- *Additional requirement for those who conduct delivery observations:* must be pursuing or graduating with a (1) Medical (2) KRCN Nursing or BscN Degree within the last 2 years, and experience in maternal and newborn care (medical, nursing and midwifery schools should be accredited by the relevant national bodies in Kenya.)

The enumerators will further receive specific in-depth training by IPA staff with clinical expertise on ethics and proper conduct expected while operating in a maternity ward. This will prepare them for how to react in various scenarios to maintain the highest ethical standards.

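### The emergency rule for delivery observers leaves every response optional and requires no observer to alert a clinician (Protocol 5.7, Delivery observations, items 4a and 4b)

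*Protocol*

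**What the plan says.** Section 5.7, Delivery observations, item 4 is the protocol's rule for emergencies. Item 4a makes non-intervention the default, with an exception for life-threatening emergencies in which the observer's involvement could help directly. It continues that, should an observer "observe gross mismanagement of a patient and he/she feels that the situation is life threatening, the enumerator may offer advice and/or assistance".

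Item 4b governs those who intervene: "They must be medically qualified to intervene in the specific situation, that is, have had the necessary training to be qualified to provide care". Where possible, "the enumerator should call the study team leader for advice on the way forward before intervening". Instances of assistance are to be documented, and observers are to keep reminding staff that "they are only observers and not present to provide care or assistance".

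The Enumerators list of staff qualifications, before section 5, says that delivery observers "must be pursuing or graduating with a (1) Medical (2) KRCN Nursing or BscN Degree within the last 2 years", and it also asks for experience in maternal and newborn care. The same list promises in-depth training by staff with clinical expertise, including how to react in different scenarios, but does not set out its content.

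Two lines of item 3 also touch the point. Under 3a, each consenting woman is told that the enumerators "will not be giving any care to her during the duration of her delivery, but will only be present as observers". Under 3b, "Enumerators will avoid speaking to patients or health workers, and will avoid sudden movements that may draw any attention".

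**The concern.** The study places a person with medical training beside each observed delivery. If that person sees a woman or newborn in danger of death and the attending staff have not noticed, or are not responding, the least to be expected is that they say so. Raising an alarm needs no licence to treat, so the qualification test in 4b is no reason to leave it out.

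The situation is foreseeable. Section 16.2 assumes an average quality index of 0.58 in control facilities, so many recommended steps are expected to be missed in front of observers. A missed step is not in itself an emergency, but some emergencies will arise in that setting. What is at stake is the safety of observed women and newborns, not the estimate of the treatment effect.

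**Working it through.** No arithmetic applies. The check is whether an observer who recognises a life-threatening event and says nothing breaks any line of the protocol.

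**Step 1: what item 4 permits and requires.**

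| Act | Observer qualified for the situation | Observer not so qualified |
|---|---|---|
| Alert a clinician on the ward | Not forbidden, not required | Not forbidden, not required |
| Offer advice (4a) | Optional | Optional on the wording of 4a, if advice is not counted as intervening under 4b |
| Intervene in care (4b) | Optional | Barred |
| Call the study team leader (4b) | Should, if possible, before intervening | No instruction, since the call is tied to intervening |
| Document (4b) | When assistance was offered | When assistance was offered |

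No cell contains a required response at the bedside.

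**Step 2: can an observer fall in the right-hand column?** Yes. The staffing list accepts people still pursuing a degree. Experience in maternal and newborn care narrows the group, but 4b asks for the training needed for the specific situation, which a student may lack.

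**Step 3: does another section supply the duty?**
- Section 3.3 has study managers report issues to the investigators within 24 hours. That is reporting after the event.
- Section 5.13 describes management meetings and data monitoring.
- Section 12.1 lists discomfort, confidentiality, infection and distress as risks. It does not address an emergency seen by an observer.
- Section 20.1 has enumerators notify the field manager at once, but only of events that arise from the research itself, and the route runs to the investigators and ethics boards.
- The Enumerators list promises scenario training without stating a rule.

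None of these brings a clinician to the bedside.

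**Step 4: result.** An observer who sees the danger and stays silent breaks no line of the protocol. The gap is a missing instruction, not a prohibition.

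**The case against.** The strongest reply is that the protocol already has a workable emergency rule and that stronger readings of its wording fail. Much of this stands.

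- A reader might infer that an unqualified observer has no permitted act. The text does not support that. Advice under 4a is open to any enumerator, and 4b restricts only those who intervene. Telling staff that a woman is bleeding is not providing care.
- A reader might infer that 3b imposes silence in an emergency. It does not. Item 3 concerns routine data collection, item 4 is the emergency exception to it, and 4b itself has observers speak to staff.
- A reader might infer that the statement to women in 3a contradicts 4a. Item 4b largely reconciles them, because anyone who steps in does so as a clinician and not as a researcher. An exception in 3a would be clearer wording, no more.
- The call to the team leader applies only where possible, so it does not block urgent help.
- Observers must have relevant experience and will be trained. The training materials are not shown and may contain an alert rule.
- An alert may change the care that is being measured. Item 4a already accepts this for advice and assistance.

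What remains is the difference between *may* and *must*. None of these replies creates a duty to alert, and training should follow a rule stated in the protocol.

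**Conclusion.** The point holds as a cheap improvement to patient safety. The protocol fixes a permissive rule where a mandatory alert would be better, and a silent observer complies with it as written.

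The size cannot be put in numbers. A reader might multiply the national death rates in section 2.1 by the 4,800 planned observations, but the result would not measure this gap. The documents do not give the share of deaths that fall while an observer is present, the share of deliveries watched by an observer who does not meet 4b, or how often staff are unaware of a danger that the observer has recognised. That last quantity decides the benefit of an alert.

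The conclusion rests on the protocol text alone. If the training materials already contain the duty, the remaining task is to write it into item 4.

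**What to change.** 1. Add to 4a: *Any observer who believes a woman or newborn is in danger of death must at once tell the attending or most senior clinician on duty, whether or not the observer is qualified to assist.* The trigger is danger, so the observer need not first judge the care to be grossly mismanaged.
2. Add to 4b: *The call to the study team leader must not delay this alert.*
3. Extend the documentation in 4b to alerts, with the time of each.

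Hands-on help stays limited to qualified observers. As an optional clarification, the statement to women in 3a can carry an exception for life-threatening emergencies.

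The cost is three short additions and one point in observer training, before endline observation starts. The downside is that an alert may change care in that delivery. Recording the time keeps such deliveries identifiable, and their handling in the quality index can be left to the statistical analysis plan.

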**5.8. Does the study involve the use of deception and/or incomplete disclosure?**

☒ **No** ☐ **Yes:** *If yes, explain the use of deception/incomplete disclosure and describe why it is necessary to achieve the goals of the study.*

**5.9. When all research-related study procedures are complete, are there plans for long-term follow up?**

☒ **No** ☐ **Yes:** *If yes, indicate what data will be collected during this period.*

**5.10. Does the study involve the collection of specimens (e.g. blood, cells, tissues, fluids, secretions, recombinant or synthetic nucleic acids, biological toxins, bacteria, virus, fungi, etc.)**

☒ **No** ☐ **Yes:** *If yes, indicate the [COMS Registration Number](#) or plans to obtain COMS approval.*

**5.11. Does the study involve the use of existing data, documents, records, and/or specimens for secondary analysis?**

☐ **No** ☒ **Yes:** *If yes, indicate how, when, where, and from whom data, documents, records, and/or specimens will be obtained.*

Enumerators will use the Register Data Form to extract data from registers in consultation with facility in-charges and head midwives. These registers are physical books kept at health facilities. The data will cover the entire period from 12-month prior to the baseline up to 12 months after the endline. Facility registers will not leave study facilities. The data extracted from these registers will be shared via Harvard Dropbox with the Harvard study team.

The study team will also use administrative program data collected by Jacaranda Health as part of the process evaluation to assess the implementation of the intervention. The data will be shared by Jacaranda Health with the study team.

**5.12. Are there provisions for medical and/or psychological support resources available to participants (e.g., in the event of incidental findings, research-related stress)?**

☐ **No** ☒ **Yes:** *If yes, describe the provisions and their availability.*

For participants in the patient surveys, in cases of stillbirth, miscarriage, or infant loss, the study team will inform participants about the option to contact "Still A Mum," a hotline that provides psychological support.

**5.13. Describe the data and safety monitoring plan for the study. This plan should outline how study progress will be monitored throughout the lifecycle of the research to ensure the safety of subjects, as well as the integrity and confidentiality of data.**

Investigators at Harvard will hold regular management-level meetings/calls with implementation partners in Kenya to discuss unexpected negative outcomes, interim results, protocol modifications, data monitoring, etc. In-person oversight from the management team will be ongoing throughout the study. The Research Manager at IPA will stay in frequent communication with the investigators about any issues related to data quality, adverse events and protocol modifications.

All survey data will be submitted on a daily basis to the SurveyCTO encrypted server and downloaded, backed up, and maintained on a secure, encrypted server managed by IPA. The data will be stored in password protected directories. Data on patients and health workers will be stripped of their identifying information and subjects will be given an alphanumeric code which will be used to identify them. The MS-Excel file with the key to the code of names associated with their respective alphanumeric codes will be kept on an electronic storage medium (ex. flash drive) and will be kept in a locked storage unit. Only the researchers and assistants associated with this study will have access to this document. All electronic data will be stored on an encrypted, secure online server and password protected. Computers holding subject data will also be password protected. A back-up drive containing a copy of all the data will be securely kept in a separate location.

**5.14. Are there any anticipated circumstances under which participants will be withdrawn from the research without their consent?**

☒ **No** ☐ **Yes:** *If yes, describe the circumstances for withdrawal as well any associated procedures to ensure orderly termination, appropriate referrals, and/or follow-up care.*

**6. Recruitment Methods** ☐ **N/A.** *Skip to next section.*

*Upload recruitment materials to the "Local-Site Documents" page in ESTR.*

**6.1. Indicate how, when, where, and by whom participants will be recruited. Provide a list of materials used to recruit participants, e.g., emails, posters, and/or scripts here.**

Participants will be recruited as follows. Recruitment scripts are attached to this application.

Health facilities: Prior to beginning work in each county, an approval letter will be signed by the county health director. A research team member will meet with the medical supervisor or maternity in-charge at each facility, present a copy of the letter, and discuss the study. This will only occur in the baseline.

**Health workers:** At each health facility and prior to conducting consent, nurses and midwives who work in the maternity wards will be recruited into the study by an enumerator for health worker interviews. In the endline, in addition to health worker interviews, other medical providers at maternity ward will be recruited into the study by an enumerator for delivery observation.

**Women giving birth:** We will recruit women at admission, a time when they are stable during labor, or discharge prior to conducting consent by an enumerator. This will only occur in the endline.

**Women receiving antenatal care:** At each facility and prior to conducting consent, women receiving antenatal care will be recruited into the study by an enumerator. This will only occur in the baseline.

